#### Outcomes

Mode of delivery will be ascertained from the medical records to measure the primary outcome. Labour and delivery outcomes, perineal trauma, blood loss, duration of hospitalisation, short term neonatal outcomes, admission to the neonatal ICU, maternal or neonatal readmission to the same institution and other components of the combined secondary outcomes will be ascertained by a study investigator not involved in clinical care, using the medical records and by contacting participants’ clinicians for further information if required. Maternal depression, health-related quality of life (SF-12), birth satisfaction (visual analogue score), maternal or neonatal readmission to another institution, ongoing breastfeeding, pelvic floor symptoms and components of the combined secondary outcomes will be collected by structured maternal questionnaires at six weeks, six months and 12 months post-delivery, as outlined in section Outcomes. Questionnaires will be completed by mail-out, online via the trial website and by telephone, depending on the participants’ preferences (Fig. 1, Table 2). Data collectors will be unaware of the treatment allocation at all times.

As the primary outcome is mode of delivery and randomisation occurs during the second stage of labour, we expect 100% ascertainment for the primary outcome. Study investigators will perform site visits about four times per year to promote recruitment, provide education for clinical staff and site investigators and audit of centre medical records to verify accuracy of data collected by sites. Participants will receive a telephone call at each time point by research staff not involved in their care to ask their preference for follow-up. Unless she declines further participation, each participant will receive a reminder telephone call, and will be offered completion of the questionnaire by telephone if they feel they cannot complete it by mail or online.

#### Data management

Data collected will be entered into a registered electronic database by research staff blinded to treatment allocation who are not involved in the clinical care of participants. Hardcopies of participants’ data will be stored in a locked office. The electronic database will include the study identification number, but no directly identifying data such as medical record number, date of birth or personal address. The de-identified database will be backed up on a server at Royal Prince Alfred Hospital. Data linking identifying details to the study number will be kept at a separate location in a locked filing cabinet. At the end of the study, data will be kept in a locked filing cabinet, and de-identified electronic data will be kept on a portable medium, such as a USB drive, in a separate secure location at Royal Prince Alfred Hospital. All electronic data will be checked for accuracy by a second member of the research team, and any apparent data entry errors will be discussed by the primary investigators and investigated and/or corrected as required.

#### Analysis

Analysis will be on an intention-to-treat basis (according to treatment allocation), including withdrawals and losses to follow-up. Losses to follow-up for the primary outcome are not expected because randomisation will occur at full dilatation and the primary outcome is the mode of delivery. The results will be reported according to the Consolidated Standards for Reporting Trials (CONSORT) guidelines.

Demographics and other potential confounders will be compared by treatment allocation in a univariate analysis. Categorical outcome measures will be compared by proportions (chi-squared test), means for normally distributed data (t-test) or rank order for non-normally distributed data (Mann-Whitney U test).

A logistic regression analysis of treatment allocation and other variables on the primary outcome measure, operative delivery, will be performed. The following variables will be considered for the logistic regression model: maternal body mass index, maternal age, maternal height, maternal ethnicity, gestation, induction of labour, gestational diabetes, neonatal gender and RCOG CTG classification in the second stage of labour. Parity, study site and the presence of epidural for intrapartum analgesia at the time of randomisation will not be included because randomisation is stratified for these variables. Only variables where *P* <0.25 in the univariate regression will be included in the multivariate model. Continuous variables that do not show a linear association with the logit function will be divided into quartiles and treated as categorical. Interaction terms will be considered for treatment allocation versus each of the other variables and, where clinically appropriate, between non-treatment variables. *P* <0.01 will be considered evidence of interaction. Terms will be excluded from the model in a stepwise backward manner until all remaining terms are both statistically significant (*P* <0.05) and clinically significant (that is, removal of the term results in a clinically significant change in the estimate of the odds ratio of treatment allocation for the primary outcome). The analysis will be performed using SAS 9.2 (or a more recent version of SAS, Statistical Analysis Software. Cary, USA).

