### Trial design

The TURN-OUT trial is designed as a superiority, double blind, multicentre, randomised, controlled clinical trial with two parallel groups and a primary endpoint of fetal mode of delivery at birth. Randomization will be performed as block randomization with a 1:1 allocation.

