### Intervention

Manual rotation is performed at full dilatation (when the woman has the first urge to push or after one hour, whichever occurs first) if the fetal position is OT. The technique employed will be at the discretion of the operator performing the procedure. The intervention will be performed by obstetricians or midwives who are experienced in performing a manual rotation and have performed at least 20 procedures. All operators will complete a questionnaire outlining their technique and experience.

With the membranes ruptured, a vaginal examination is performed and the woman is asked to bear down. Constant pressure is exerted with the index finger against the lambdoid suture to rotate fetal head. This may take two to three contractions and the position is commonly held for two contractions while the woman bears down to reduce the risk of reverting back to the OP position. Alternatively, the examiner places two fingers behind the fetal ear or the entire hand behind the occiput and applies constant flexion and rotation to the fetal head.

For the purposes of the TURN-OUT Trial, the procedure will be described as a ‘digital rotation’ if only the fingers are used, and as a ‘manual rotation’ if the whole hand is used.

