### Outcomes

#### Primary outcome

The primary outcome will be operative delivery (vacuum, forceps and/or caesarean section). Operative delivery will be performed at the discretion of the clinicians caring for the woman who will be blinded to the treatment allocation. In Australia, most obstetricians perform caesarean section and instrumental deliveries in line with the ACOG recommendations [10]. That is, operative delivery for prolonged second stage of labour is considered after one hour of full dilatation for parous women without an epidural, two hours for parous women with an epidural or nulliparous women without an epidural, and three hours for nulliparous women with an epidural. Operative delivery is also performed for suspected fetal compromise manifested as a pathological cardiotocograph (especially prolonged decelerations, variability <5 for more than 90 minutes or baseline >160 beats per minutes), fetal scalp lactate >4.8 mmol/L or pH <7.20.

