### Sample size

The sample size (416) was calculated on the basis of the primary outcome. This power calculation is based on our prospective cohort of women with a fetus in the OT position [3], and our surveys of obstetricians and midwives who would perform a manual rotation if it reduced the rate of operative delivery by about 18% [10, 11]. To detect a reduction in operative delivery from 49% in controls to 35% in the intervention group, a sample size of 208 in each group (total = 416) will be required for α = 0.05 (two-tailed), β = 0.20 (power = 80%) (calculated using Epi Info™ version 3.3.2, Centers for Disease Control and Prevention, Atlanta, USA).

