**Fig. 1 Fig1:**
[figure not shown]
An overview of the conduct of the TURN-OUT trial. Losses to follow-up for the primary outcome are not expected, as it occurs within hours of randomisation and the mode of delivery (caesarean, vacuum, forceps and normal birth) is easily obtained from the hospital records

**Table 2 Tab2:** The TURN-OUT study timeline for the schedule of enrolment, allocation and follow-up

	Enrolment		Allocation	Post-allocation				
Time point	35-37 weeks gestation	1st stage labour	During 2nd stage of labour	Immediately after allocation	1-3 days	6 weeks	6 months	12 months
1st eligibility screen	X							
2^nd^ eligibility screen		X						
Informed consent	X	X						
Allocation			X					
Intervention				X				
Assessments:								
Labour and delivery			X	X	X			
Operative delivery					X			
Perineal outcome					X			
Blood loss					X			
Maternal complications					X	X		
Hospital stay					X			
Readmission						X		
Neonatal outcomes					X	X		
Neonatal ICU admission(s)					X	X		
Satisfaction with birth						X		
Breastfeeding						X	X	X
Health-related quality of life						X	X	X
Pelvic floor						X	X	X
Depression						X	X	X

An ultrasound will be performed at full dilatation by the clinician caring for the woman, and the findings will be recorded on a data sheet immediately afterwards. An hour after full dilatation or at the first urge to push, a study investigator (with no clinical responsibility for the woman in the trial) will confirm the OT position by a second (pre-procedure) bedside ultrasound. If the fetal position is still OT and the woman still wishes to participate then the study investigator will randomise the woman to either manual or sham rotation. The treatment allocation will be recorded on a randomisation sheet, which the investigator will keep on their person and not show to any of the participant’s medical staff. After the manual rotation or sham has been performed the ultrasound will be repeated, ensuring that the woman and her medical staff do not see the screen. The investigator will leave and the woman will have her usual care from this point onwards. The investigator will record the findings on vaginal examination, details of the procedure and post-procedure ultrasound findings on the same data sheet as the pre-procedure ultrasound. The study investigator will keep this data sheet on their person and not show it to any of the participants’ medical staff.

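### The supporting adjusted regression may include a second-stage CTG classification that is not limited to readings before randomisation, so the adjusted treatment effect can be distorted

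*Protocol article*

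**What the plan says.** In the protocol article, the Analysis section lists the variables to be considered for the logistic regression of operative delivery. The list ends with "neonatal gender and RCOG CTG classification in the second stage of labour". No time point relative to randomisation is given. The next sentence, on the stratification factors, does tie epidural status to the moment of randomisation.

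Candidates enter the multivariable model if univariate P <0.25. They stay if P <0.05 and if removing them changes the treatment odds ratio by a clinically significant amount.

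The Intervention section times the rotation at full dilatation, "when the woman has the first urge to push or after one hour, whichever occurs first". The study conduct text after Fig. 1 times the pre-procedure ultrasound and randomisation in the same way: "An hour after full dilatation or at the first urge to push, a study investigator" confirms the position and then randomises. Randomization and allocation concealment adds that randomisation immediately precedes the procedure.

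Under Primary outcome the article says: "Operative delivery is also performed for suspected fetal compromise manifested as a pathological cardiotocograph". Under Other outcomes, operative delivery is also to be reported by indication, and suspected fetal compromise is defined there partly by a pathological CTG.

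The Abstract gives the chi-squared test as the comparison for the primary outcome. The logistic regression comes in addition, to account for potential confounders.

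**The concern.** The second stage runs from full dilatation to birth, and randomisation falls inside it. A classification covering the second stage can therefore draw on tracing from before the procedure, from after it, or from both.

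A CTG read after the rotation or sham is not a baseline characteristic. If rotation changes fetal heart-rate patterns or the length of labour, the CTG carries part of the treatment effect. Because it is also a reason for operative delivery, adjusting for it removes that part. A benefit acting through better fetal condition would be understated. If rotation worsened the CTG, adjustment would make rotation look better than it is.

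The Epidemiology section cites adjustment for second-stage CTG in an observational cohort comparing fetal positions. That does not carry over to a randomised comparison, where a variable that treatment can change is not a confounder.

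What is at stake is the only adjusted estimate that the article describes for the primary outcome.

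**Working it through.** **1. The plan's own figure.** Sample size states "To detect a reduction in operative delivery from 49% in controls to 35% in the intervention group" with "α = 0.05 (two-tailed), β = 0.20 (power = 80"%), and that "a sample size of 208 in each group (total = 416) will be required". Trial design states: "Randomization will be performed as block randomization with a 1:1 allocation".

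- Mean proportion = (0.49 + 0.35)/2 = 0.42.
- Without continuity correction: n = [1.960 × √(2 × 0.42 × 0.58) + 0.842 × √(0.49 × 0.51 + 0.35 × 0.65)]² / 0.14² = 193.9, so 194 per arm (388 in total).
- With continuity correction: (193.9/4) × [1 + √(1 + 4/(193.9 × 0.14))]² = 207.96, so 208 per arm and 416 in total.

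The stated figure is reproduced. It rests on the unadjusted comparison, so the covariate does not affect it.

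**2. The target effect.** Risk difference = 0.35 - 0.49 = -14.0 points. Odds ratio = (0.35/0.65)/(0.49/0.51) = 0.560.

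**3. Assumptions.** The article gives no CTG rates by arm and no CTG odds ratio for operative delivery. Assumed here: a binary abnormal CTG read after randomisation, at 20% or 30% by arm, with a CTG odds ratio of 3 to 6. Total rates are held at 49% and 35%. For each arm, the intercept k solves (1 - m) × expit(k) + m × expit(k + ln OR) = total rate, where m is that arm's abnormal-CTG rate. The adjusted OR is exp(k for rotation - k for sham). The adjusted risk difference is standardised to the pooled CTG distribution.

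**4. One case in full: abnormal CTG 30% sham, 20% rotation, CTG odds ratio 6.**

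- Sham: operative delivery 36.7% with normal CTG and 77.7% with abnormal. Check: 0.7 × 0.367 + 0.3 × 0.777 = 0.49.
- Rotation: 26.6% and 68.5%. Check: 0.8 × 0.266 + 0.2 × 0.685 = 0.35.
- Adjusted OR = (0.2662/0.7338)/(0.3671/0.6329) = 0.625.
- Standardised at 25% abnormal: sham 0.75 × 0.3671 + 0.25 × 0.7768 = 0.4695; rotation 0.75 × 0.2662 + 0.25 × 0.6852 = 0.3710 (0.3709 before rounding the inputs). The difference is -9.9 points.

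**5. Results for CTG odds ratio 3 and 6.**

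| Abnormal CTG, sham vs rotation | Adjusted OR | Adjusted risk difference (points) |
|---|---|---|
| 30% vs 30% (no effect on CTG) | 0.540, 0.506 | -14.0, -14.0 |
| 30% vs 20% (rotation improves CTG) | 0.609, 0.625 | -11.4, -9.9 |
| 20% vs 30% (rotation worsens CTG) | 0.483, 0.421 | -16.6, -18.0 |

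The first row shows why the risk difference is the cleaner measure. The OR moves away from 0.560 with no bias at all, because a conditional odds ratio differs from a marginal one (non-collapsibility). The risk difference stays at -14.0.

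**6. No total effect.** With both arms at 49% and abnormal CTG rising from 20% (sham) to 30% (rotation), the adjusted OR is 0.894 (CTG odds ratio 3) or 0.832 (CTG odds ratio 6). A balanced baseline CTG would leave it at 1.00.

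**7. Would the term survive selection?** In 2,000 simulated trials of 208 per arm with a CTG odds ratio of 6, CTG passed both P-value rules in essentially every trial. The article does not quantify the change-in-OR rule. Taking a 10% change as the threshold (assumed), CTG met it in 51% of trials at 30% vs 30%, 23% at 30% vs 25%, 58% at 30% vs 20% and 94% at 30% vs 15%. The rule does not screen out a mediator, and it keeps a strong one nearly always. At 30% vs 20%, power of the treatment term fell from about 83% to 59%.

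**The case against.** A reader might infer that the covariate is measured after randomisation and that the primary analysis is therefore biased. The article supports neither.

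- **Timing.** The second stage can begin up to an hour before randomisation, and Exclusion criteria already use the RCOG classification, so a baseline reading is a possible meaning. This stands: post-randomisation tracing is permitted, not stated. It does not remove the point, because the article names the variable and its window and leaves that window open past randomisation. That is a stated choice, not a detail left to a statistical analysis plan.
- **Bias is conditional.** The variables are only to be considered, and nothing in the article shows that rotation changes the CTG. Table 1 has no CTG outcome, and its estimates for cord pH (0.55, 0.15-2.01) and base excess (1.21, 0.64-2.30) are inconclusive. This stands. If rotation leaves the CTG unchanged, the risk difference is undistorted, as the first row of the table shows.
- **Reach.** The chi-squared test is the stated comparison for the primary outcome, and the regression is additional. Operative delivery by indication and serious neonatal morbidity are also reported, and adverse events go to the monitoring committee. This stands, so the adjusted model could not by itself conceal harm.
- **Size of the null case.** It requires a direct benefit that exactly cancels harm through the CTG. The standard error of the unadjusted log OR is √(2/(208 × 0.49 × 0.51)) = 0.196. The shifts ln 0.894 = -0.112 and ln 0.832 = -0.184 are thus about 0.6 and 0.9 standard errors, and would rarely be declared a benefit. This also stands.

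**Conclusion.** The point holds for the supporting logistic regression. The CTG covariate has no fixed time point and, as worded, can include tracing after the procedure. If such tracing is used, the term is retained and rotation affects the CTG, the adjusted effect is distorted. With 10-point shifts in abnormal CTG and a CTG odds ratio of 3 to 6, all assumed, the adjusted risk difference is off by about 2.6 to 4.1 points on a true 14.0: towards no effect if rotation improves the CTG, away from it if rotation worsens it. These figures illustrate the size and are not predictions. The intention-to-treat chi-squared comparison and the sample size stand. Severity: should be fixed.

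**What to change.** Define the covariate as the last CTG classification before randomisation, or drop it. Eligibility screening already requires a CTG assessment. Only some pathological tracings are excluded at entry, so the classification still varies at baseline. Add a sentence that no variable which treatment can affect after randomisation enters the treatment-effect model. Report post-procedure CTG by arm descriptively, so that any effect of rotation on fetal condition is seen and not adjusted away.

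The cost is a line or two in the analysis text and a time point for the CTG field on the data sheet. Trial status reports 128 participants recruited so far. For those already randomised, the pre-randomisation reading can be taken from the tracing where it has been kept; where that is not feasible, the variable can be dropped. The sample size and the main comparison do not change.

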**Methods/Design:**

Eligible participants will be ≥37 weeks pregnant, with a singleton pregnancy, and a cephalic presentation in the occiput transverse position on transabdominal ultrasound early in the second stage of labour. Based on a background risk of operative delivery of 49%, for a reduction to 35%, an alpha value of 0.05 and a beta value of 0.2, 416 participants will need to be enrolled. Participants will be randomised to either prophylactic manual rotation or a sham procedure. The primary outcome will be operative delivery. Secondary outcomes will be caesarean section, significant maternal mortality and morbidity, and significant perinatal mortality and morbidity.

Analysis will be on an intention-to-treat basis. Primary and secondary outcomes will be compared using a chi-squared test. A logistic regression for the primary outcome will be undertaken to account for potential confounders. This study has been approved by the Ethics Review Committee (RPAH Zone) of the Sydney Local Health District, Sydney, Australia, (protocol number: X110410).

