### Randomization and allocation concealment

Randomization will be stratified by parity, hospital site and epidural due to the potentially strong association between operative delivery (the primary outcome) and each of these factors. Randomization will be centrally controlled using computerized sequence generation, which can be accessed 24 hours per day using a toll-free telephone line.

In order to reduce the risk of randomising an ineligible participant, randomisation will occur immediately before the intervention or sham procedure is to be performed. An example of a participant becoming ineligible would be if the fetus rotated from the OT to the OA position. Each investigator will complete a data collection form at the time the manual rotation or sham procedure is performed, outlining the treatment allocation, clinical findings and whether or not the fetus was successfully rotated.

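### Parity, site and epidural are kept out of the regression because randomisation is stratified on them; that is a reason to include them, and leaving them out costs some efficiency

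*Protocol article*

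**What the plan says.** - **Design.** Under Randomization and allocation concealment, the protocol article explains the choice of factors: "Randomization will be stratified by parity, hospital site and epidural due to the potentially strong association between operative delivery (the primary outcome) and each" of them. Trial design adds: "Randomization will be performed as block randomization with a 1:1 allocation".
- **Main comparison.** The abstract states: "Primary and secondary outcomes will be compared using a chi-squared test". The Analysis section repeats the chi-squared test for categorical outcomes and mentions no stratification.
- **Regression.** The Analysis section then describes a logistic regression of operative delivery on treatment and a list of candidate variables, chosen by a univariate screen at P<0.25 and backward elimination. Of the design factors it says: "Parity, study site and the presence of epidural for intrapartum analgesia at the time of randomisation will not be included because randomisation is stratified" on them.

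Whichever of the two is read as the primary analysis, parity, site and epidural are absent from it.

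**The concern.** Stratified blocks keep the arms balanced within each stratum, so differences in risk between strata largely cancel from the treatment comparison. An analysis that ignores the strata still counts those differences as noise, and its standard error describes a less precise design than the one that was run. Stratification is therefore a reason to carry the factors into the analysis.

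The protocol itself expects the factors to matter. It chose them for their likely relation to operative delivery. Its Primary outcome section gives time limits for considering operative delivery of one, two or three hours according to parity and epidural. Its Epidemiology section reports that the earlier cohort analysis adjusted for both.

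At stake is precision that the randomisation has already provided: a P value somewhat too large, a risk-difference interval somewhat too wide, and some power lost.

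**Working it through.** **1. The plan's sample size.** Inputs from Sample size: 49% against 35%, two-sided α 0.05, power 80%. The mean rate is 0.42 and the difference 0.14.

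n = [1.960·√(2·0.42·0.58) + 0.842·√(0.49·0.51 + 0.35·0.65)]² / 0.14² = 193.9 per arm without continuity correction.

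With the correction, n′ = (n/4)·[1 + √(1 + 4/(n·0.14))]² = 207.96, or 208 per arm and 416 in all. This matches the plan exactly. With 208 per arm the uncorrected chi-squared test has 82.7% power. No allowance for loss is needed: "we expect 100% ascertainment for the primary outcome".

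**2. How much ignoring the strata inflates the standard error.** Let w be the share and p_s the risk in stratum s, with overall risk p.
- The unadjusted test uses p(1−p) = Σw·p_s(1−p_s) + Σw(p_s−p)².
- Under stratified blocks, approximately only the first term contributes to the true variance.
- The standard error is too large by k = √[p(1−p) / Σw·p_s(1−p_s)], and the true type I error is about 2[1−Φ(1.96k)].

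Assumptions not in the documents: 70% nulliparous, 60% with epidural, the two independent, and no site effect in this step. The shares are then 0.12 (parous, no epidural), 0.18 (parous, epidural), 0.28 (nulliparous, no epidural) and 0.42 (nulliparous, epidural). With 49% in both arms, p(1−p) = 0.2499.

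- Odds ratios 2 (nulliparity) and 1.5 (epidural): stratum risks 31.6%, 40.9%, 48.0% and 58.1%. Between-stratum variance is 0.0083, leaving 0.2416. k = √(0.2499/0.2416) = 1.017; type I error about 4.6%.
- Odds ratios 6 and 3: stratum risks 11.9%, 28.9%, 44.9% and 70.9%. Between-stratum variance is 0.0444, leaving 0.2055. k = √(0.2499/0.2055) = 1.103; type I error about 3.1%.

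In the second case the half-width of the 95% interval for the risk difference is 1.96·√(4·0.2499/416) = 9.6 points, where 1.96·√(4·0.2055/416) = 8.7 would do.

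**3. Simulation of the whole design.** 416 women, 24 strata (parity × epidural × six equal sites), permuted blocks of 4, site log-odds SD 0 to 0.4, 6,000 replicates per row. Each cell gives unadjusted chi-squared (no continuity correction) / stratified Mantel-Haenszel / logistic with parity, epidural and site.

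| Assumed OR, nulliparity and epidural | Type I error, % | Power for 49% vs 35%, % |
|---|---|---|
| 1 and 1 (no site effect) | 5.1 / 5.0 / 5.1 | 83.1 / 82.8 / 83.3 |
| 2 and 1.5 | 4.8 / 5.0 / 5.2 | 82.8 / 83.4 / 84.1 |
| 2 and 2 | 4.2 / 5.0 / 5.1 | 83.7 / 85.1 / 85.5 |
| 3 and 2 | 4.1 / 5.1 / 5.3 | 83.9 / 85.8 / 86.3 |
| 4 and 3 | 3.3 / 4.5 / 4.6 | 84.4 / 87.8 / 88.1 |
| 6 and 3 | 3.1 / 5.0 / 5.2 | 85.7 / 89.5 / 89.8 |
| 8 and 4 | 2.6 / 4.7 / 4.9 | 85.2 / 90.3 / 90.8 |

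The Monte Carlo standard error is about 0.3 points for type I error and 0.5 for power. Two smaller simulations agree in direction. With 3,000 trials, unadjusted type I error was 4.4% at 2 and 1.5 and 3.4% at 6 and 3. With 1,500 trials it was about 4.1% and 2.1%, with risk-difference standard errors about 2% to 10% too large, in line with step 2.

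**The case against.** The case for leaving the plan alone has real force.

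- **Nothing is invalid.** A reader might infer that the primary test is wrong or underpowered. It is not. Its error is on the safe side, the marginal comparison is unbiased, and unadjusted power exceeds 80% in every scenario. This stands, and it sets the grade.
- **The stated reason governs only the regression.** The plan never says that stratification is why it uses a plain chi-squared test. Deleting the sentence alone would leave that test unchanged. This stands, so the fix must name the primary test as well.
- **The size rests on assumptions.** The documents give no odds ratios, stratum shares or block size. The Discussion expects women with regional analgesia to be consented more readily and rapid labours to be missed, so the sample may be more uniform. With 85% nulliparous and 85% epidural, a further simulation gave a gain of about 1 point at odds ratios 2 and 1.5, and 2 to 3 points at 6 and 3. This stands, and the gain should be read as a range.
- **These need not be the strongest predictors.** The protocol calls the association potentially strong but ranks nothing. Its candidate list also includes second-stage CTG classification, and a pathological CTG is one of its own indications for operative delivery. A claim that the model drops the best predictors and keeps weaker ones is unsupported.
- **The odds-ratio interval would not narrow.** Adjustment raises the standard error of the log odds ratio from about 0.20 to 0.21–0.23. Power rises because the conditional odds ratio lies further from 1. The too-wide interval is that of the risk difference. An unadjusted odds ratio is a legitimate marginal quantity, not an error.

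None of this rescues the reason given. When the strata do not predict the outcome, adjustment costs essentially nothing.

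**Conclusion.** The point holds as one of efficiency. The reason for excluding parity, site and epidural is mistaken, and no stated analysis of operative delivery reflects the stratified design. For assumed odds ratios of 2 and 1.5 up to 6 and 3, the unadjusted test has a true type I error of about 4.4% down to 2–3.5%. It gives up about 1 to 5 points of power, and its risk-difference standard error is about 2% to 10% too large. With strata unrelated to the outcome the loss is nil.

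The figures depend on the assumed odds ratios, shares, equal sites and blocks of 4; the direction does not, provided that the strata predict the outcome. Because the exclusion also keeps these factors out of the treatment interactions, a reader might count that as a further defect. In a trial sized for the main effect, such interaction tests are optional. Grade: a free improvement, not a must-fix.

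**What to change.** 1. Delete the sentence in the Analysis section that excludes the three factors.
2. Name one primary test of operative delivery: either a Mantel-Haenszel test stratified by parity, epidural at randomisation and site, or a logistic model with treatment and these three factors forced in, exempt from the P<0.25 screen and from backward elimination.
3. Report a stratified or standardised risk difference with its 95% CI beside the conditional odds ratio.
4. Keep the unadjusted chi-squared test as supportive.

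Stratified tests for the binary secondary outcomes and treatment interactions with parity and epidural are optional.

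The cost is wording only. The factors are needed at randomisation and so are already recorded, and the sample size does not change. The article reports 128 women recruited and masked statisticians, so the change is credible if it is fixed before unblinding.
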